## **6. Ethical consideration**

The study protocol will be submitted to Tikur Anbessa Specialized Hospital, St. Pauls' Millennium Medical College, AHRI Institutional Ethical Review Board and National Ethics Review Board of Ethiopia and icddr, b IRB for ethical approval. Written informed consent will be obtained from parent or guardian of each study participants.

All data from the study participants will be kept in a locked cabinet at AHRI and will only be accessed by the study investigators. During publication, all patient identifiers will be removed in order to keep confidentiality.

Data Safety monitoring board (DSMB) will be established which will consist of one Pediatrician, one statistician, one Epidemiologist and Pediatric Intensivist who have knowledge on bubble CPAP. Results will be reported to the DSMB every 3 months and interim analysis will be done at 6 months of Stage III trial after which actions will be taken accordingly. All severe adverse events and deaths will be communicated to the DSMB within 24 hours.

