## **12. Final reporting, dissemination and publication**

After the end of the study the results will be reported nationally and internationally by attending national and international scientific conferences and by arranging dissemination programs in Ethiopia, Bangladesh and other developing countries. Additionally we will publish the findings in international peer reviewed journal(s). Both AHRI and icddr,b will be the owner of the collected data. However, all investigators will have access to the data and those fulfilling international authorship criteria will be included as authors in manuscripts reporting the study results. For the main manuscript, the study PIs (Drs [name] and [name]) of this study will be the co-first authors of the main manuscript. One investigator from the Ethiopia and one from icddr,b (Professor [name]) will be the co-senior authors of this manuscript written from this study. If there will be more than one manuscript from this study, first authorship will be discussed and allocated according to international standards of authorship before preparing the draft.

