| 2. Customers: who are we directly trying to impact: clinicians, researchers?             | Clinicians, researchers                                | Significant role in implementing study activities following the design of the protocol. Administrative, logistic support and scientific guidance will be ensured by them through continued monitoring. Otherwise the actual outcome may be hampered. | Frequent visits of clinicians and researchers in the study hospitals and spend time as much as possible to observe implementation of intervention and gather real life experiences through interaction with relevant personnel. Monthly meeting can be arranged with the participation of researchers and clinicians to discuss together about study progress, findings and other related issues. |
| 3. Commissioner s: payors (individuals, insurers, government)                            | Government personnel (e.g., Head in district hospital) | Need to inform about the study to create an amicable environment for implementing the proposed intervention in government hospital facilities, although, they might not have a direct role to implement the study.                                   | Clinicians and researchers will arrange a meeting at the very beginning of the study implementation to create awareness about the study objectives, implementation activities and process. This can help to get a formal permission and their valuable guidance for successful implementation of                                                                                                  |

|                                                                                                                                                |                                                                                                                                                                                     |                                                                                                                                                                                                                                                                                            |                                                                                                                                                                                                                                                                                   |

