| 7. Commentators : opinion leaders for the customers eg community leaders, press, individuals on social media | Individuals (e.g., patients caregivers, physicians, nurses, civil surgeon, UH&FPO) | Their opinion may justify the intervention as details as possible from their insights and multiple point of views.                                                                                                                           | They will express their opinion to the study experts and trained researchers concurrently during conducting interviews and observation.                                                                                                                                                                                                                                                                                                       |
| 8. Champions: eg national policy makers, national offices of agencies eg WHO, World Bank                     | Renowned paediatricians', senior physicians, govt decision makers                  | Their opinion requires creating an enabling policy environment to implement the effectiveness trail within the existing health system. Because, they have influential role in decision making to extend the intervention in other hospitals. | They would be informed by clinicians and researchers about the introduction of bubble CPAP in a meeting before implementing the CPAP. Moreover, they might be invited at mid or end time of study period in dissemination meeting to participate in discussion about key findings of the effectiveness trial, where they can provide valuable feedback and important guidance in adopting the intervention within the existing health system. |

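### Annex 15 permits Stage III findings to be discussed outside the DSMB before the trial ends, and nothing in the protocol restricts interim comparative results

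*Protocol*

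**What the plan says.** - **Annex 15, row 8 (Champions).** The group is "Renowned paediatricians', senior physicians, govt decision makers". Their optional invitation is worded as follows: "invited at mid or end time of study period in dissemination meeting to participate in discussion about key findings of the effectiveness trial". One purpose of that meeting is their "guidance in adopting the intervention within the existing health system". The row explains that "they have influential role in decision making to extend the intervention in other hospitals".
- **Annex 15, row 2 (Customers).** "Monthly meeting can be arranged with the participation of researchers and clinicians to discuss together about study progress, findings and other related issues". No stage is named, and the row does not say whether findings are pooled or shown by arm.
- **Section 6 (Ethical consideration).** "Results will be reported to the DSMB every 3 months", with an interim analysis at 6 months of Stage III.
- **Section 11 (Termination).** The DSMB decides on termination after analysing the quarterly report. The IRBs and FMHACA are informed beforehand.
- **Section 12 (Final reporting, dissemination and publication).** "After the end of the study the results will be reported nationally and internationally".
- **Section 5.2, Stage III, Primary outcome.** Treatment failure is any of: SpO2 below 85% together with respiratory distress after at least one hour; an indication for mechanical ventilation; death in hospital or within 72 hours of leaving against advice; leaving against advice while still on the study intervention.

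**The concern.** Allocation is by hospital, the two treatments are visibly different, and no blinding of treating staff or outcome assessors is described. Respiratory distress, an indication for ventilation and leaving against advice all leave room for judgement or behaviour. In such a trial, confidentiality of the interim comparison is one of the few protections against a trend influencing its own confirmation.

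Staff who hear that one arm is doing better may change when they declare failure, how they counsel a family that wants to leave, or whom they enrol. Decision makers who hear it may encourage earlier use of bubble CPAP. The first could bias the relative risk, and the second could shrink the contrast between arms. Neither could be reliably removed in the analysis, because nobody would know how much of the observed difference it explains.

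**Working it through.** **1. Does row 8 concern Stage III?** Section 5.1 and the Stage III part of section 5.2 use effectiveness for Stage III; Stages I and II test feasibility, acceptability and safety. Row 5 of the same annex names the effectiveness trial separately from formative research. Row 8 therefore refers to Stage III, and findings discussed before it ends are interim findings.

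**2. Will interim findings exist?** Yes. Section 6 requires quarterly results to the DSMB and an interim analysis at 6 months.

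**3. Is their circulation restricted?** Sections 6 and 11 say what the DSMB receives and decides. Neither says that others may not see it. Section 12 places reporting after the end of the study, while row 8 allows an earlier point. The two need reconciling.

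**4. How far does row 2 go?** It covers progress and findings. Row 4 is narrower: it covers progress, operational challenges and their solutions. Row 2 neither states nor excludes Stage III outcomes by arm.

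**5. Could attendees influence the outcome?** Section 5.3.1 makes two nurses, a general practitioner and a pediatrician the research team at each site, and section 5.3.4 trains them on the data collection tools. Row 9 says that clinicians and researchers measure the outcome. Overlap with the row 2 attendees is plausible, but it is an inference.

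**6. Illustrative size.** The protocol gives no figure for this point, so the shifts below are assumptions.

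Inputs from the Stage III sample-size paragraph: 620 per arm, failure 10% v 5%, z = 1.96, ICC 0.003, m = 103.3, printed design effect 1.52.

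*The plan's own figure.* The stated formula gives a design effect of 1 + 0.003 × (103.3 − 1) = 1.307, not 1.52. A two-proportion calculation with continuity correction gives 474 per arm, and 474 × 1.307 = 619.5, which matches 620. With 1.52 it would be 720. Both design effects are carried below.

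*Effective size per arm.* 620/1.307 = 474.4; 620/1.52 = 407.9.

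*Formula.* SE = √{[p1(1−p1) + p2(1−p2)]/n}; probability of significance = P(|Z| > 1.96) when Z has mean (p1−p2)/SE and unit variance.

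*No true effect, declared failure drifting to 11% v 9%.* The variance term is 0.0979 + 0.0819 = 0.1798.
- Design effect 1.307: SE = √(0.1798/474.4) = 0.01947; mean 0.02/0.01947 = 1.027; probability 17.7%.
- Design effect 1.52: SE = √(0.1798/407.9) = 0.02100; mean 0.953; probability 15.9%.

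A drift of half that size (10.5% v 9.5%) gives 8.1% and 7.6%.

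*Hypothetical early uptake.* Suppose 20% or 50% of control children enrolled in the second half receive bubble CPAP and have the 5% failure rate. The control rate becomes 10% − 0.10 × 5% = 9.5%, or 10% − 0.25 × 5% = 8.75%.

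| Control v bubble CPAP | Power, DE 1.307 | Power, DE 1.52 |
|---|---|---|
| 10% v 5% | 83.6% | 77.7% |
| 9.5% v 5% | 76.5% | 70.1% |
| 8.75% v 5% | 62.9% | 56.5% |

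The starting power differs from the planned 80% because this approximation has no continuity correction.

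**The case against.** **The meetings are optional, and the dissemination meeting may be at the end.** True. An unrestricted option is still a permission, and it is the permission that needs to go.

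**The middle of the study period need not be the middle of Stage III.** The 54 months from 1 July 2018 have their midpoint around October 2020, before this version's date of 3 January 2022. The timing of Stage III cannot be established from the text. This stands as a point about timing. It does not help the wording: if Stage III findings existed at that point they were interim, and if they did not, removing the option costs nothing.

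**Row 2 may mean operational or Stage I/II findings.** This stands. A reader might infer monthly review of Stage III outcomes by arm, but the row does not say so. The defect is that it does not exclude it.

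**Bedside staff are not shown to be the audience.** Row 2 clinicians make visits to the study hospitals, hospital staff are listed separately in row 6, and the row 8 audience is senior physicians and decision makers. So the overlap is not stated.

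**Control hospitals are not said to switch.** A reader might infer it from the "influential role in decision making to extend the intervention in other hospitals". That phrase names no control hospital and reads equally well as later scale-up. Section 10 requires an amendment request to the IRBs for any protocol change.

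**Section 12 does not say that results are reported only at the end.** Correct. The passages are in tension rather than in flat contradiction.

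**Confidentiality may be covered in a SAP or DSMB charter that is not shown.** Possibly. The point rests on what the annex allows, and a confidentiality rule elsewhere would then conflict with it.

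**Conclusion.** The point holds in a limited form. Row 8 expressly permits mid-study discussion of Stage III key findings with senior physicians and government decision makers. Row 2 permits monthly discussion of findings without limiting their content. No section confines interim comparative results to the DSMB. With no blinding described and some outcome components open to judgement or behaviour, this is an avoidable route to bias.

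Three stronger conclusions are not supported: that clinicians will see Stage III results by arm every month, that control hospitals will be switched, and that most of the primary outcome is subjective. On the last, death and a measured saturation threshold are part of the definition, and no component frequencies are given.

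The 16–18% false-positive probability (11% v 9%) and the power losses rest entirely on assumed shifts, 620 per arm and the two candidate design effects. They show what modest shifts could do, not what is expected. The change is worth making because the harm would be hard to detect or undo and the remedy is only wording.

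**What to change.** 1. **Annex 15, row 8:** delete the words *mid or*, so that Stage III effectiveness findings are disseminated after the end of the study, consistent with section 12.
2. **Annex 15, row 2:** state that until database lock these meetings cover recruitment, data completeness, operational challenges and Stage I/II results, with no Stage III outcomes by arm or by hospital.
3. **Section 6:** state that comparative interim results go only to the DSMB, except for the safety reporting to FMHACA in section 9 and the notices to the IRBs and FMHACA before termination in section 11. Without this exception the restriction could be read as blocking required reports, since death is both a primary-outcome component and a serious adverse event.

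The cost is a protocol amendment to two annex rows and one sentence in section 6, plus an instruction to those who run the meetings. It needs no patients, staff or analysis work.
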